#### Secondary Outcome Measures

Secondary outcome variables will be examined among sexually active participants including condom use at last sex, number of sexual partners, sex without a condom in the last 3 months and sex without contraception in the last 3 months. It is expected that 20-25% of study participants will be sexually active. The impact evaluation will also have exploratory outcome variables including parental engagement (communication and monitoring), youth substance use and substance use just prior to and/or during sex.

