## Methods/Design

### Trial Design

The study is a randomized controlled superiority trial with two parallel groups and primary endpoints of condom use self-efficacy, condom use intention, sexual and reproductive health knowledge, and delayed sexual initiation 9 months post-intervention. Block randomization will be performed with a 1:1 allocation.

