#### Primary Outcome Measures

The primary outcome variables are sexual/reproductive health knowledge, sexual initiation, condom use self-efficacy and intent to use a condom at next sex as changed from baseline to post-intervention between intervention and control participants. These variables were chosen because they are applicable to all study participants.

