### Sample Size Calculation and Statistical Analysis

Our goal is to recruit 567 youth (and their parent/trusted adult) balanced within two age groups (11–12, 13–15 and 16–19), for a total of 1134 participants (567 youth and 567 parents/trusted adults). We expect a maximum attrition rate of 25%, based on past rates in similar evaluations [18, 19, 29, 30].

Sample size estimates were based on the variables of condom use self-efficacy and sexual initiation because these confirmatory research questions apply to all study participants, and prior studies have shown them to be associated with reductions in risky sexual behavior, teen pregnancy and STI incidence [23]. We hypothesize that the RCL intervention will increase condom use self-efficacy in the intervention group compared to the control group and that the intervention group will have a lower proportion of participants who initiate sex, compared to controls, at study end line.

The condom use self-efficacy scale ranges from 1–5. Our pilot trial [18] provided data on the condom use self-efficacy score among the control group (mean = 2.6, SD = 1.0), degree of intra-team correlation (“k” = 0.12) and potential loss to follow-up over 9 months (20% average reduction in team size, i.e., from 9 down to 7.2 youths). Although this trial will utilize individual randomization, the intervention will be carried out with teams of 8–12 participants each, which will require accounting for intra-team correlation.

We will use the average of two follow-up measures of condom use self-efficacy per participant (intra-measure correlation = 0.7) to reduce error in outcome measurement [31]. To achieve 90% power to detect a theoretically meaningful between-group difference of 0.47 points on this scale over 9 months post-intervention, ~32 teams per study arm will be required. Thus, we will enroll and randomize a total of *n* = 284 participants per study arm (32 teams/arm *9 participants/team), for a total sample size of *n* = 567 participants. We have reduced the significance level used in sample size calculations to 0.0125 to account for multiplicity corrections during analyses. This same sample size will be sufficient to detect a 19.7% between-group difference, with 80% power and 0.0125 significance level, in the percent of participants who report ever having had sex. This estimate is conservative based on our past retention rates and accounts for up to 25% loss to follow-up, while adjusting for the intra-team correlation.

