This sample size will also be able to detect meaningful differences between the intervention and control groups with at least 80% power, given the assumptions listed above: 6.7% between-group difference in reproductive/sexual health knowledge score [estimating a mean score (SD) of 76% (16%) in the control group] and 20.5% between-group difference in intention to use a condom at next sex (estimating 55% in the control group).

Study hypotheses will be initially tested under an “intent-to-treat” model in which data are analyzed according to randomization assignment. We will then conduct “completer analyses” on those subjects finishing at least two-thirds of the 9 intervention sessions. Intervention impact will be evaluated by comparing primary study outcomes between intervention and control groups across the three time points: baseline, 3 and 9 months post-intervention. Initially, summary scores of outcomes will be stratified by participation in the intervention versus control groups and by time point and compared using chi-square tests (for binary or categorical outcomes), t-tests and analysis of variance (for continuous outcomes). The equivalence of the two study groups at baseline will be compared across a range of background variables. Generalized linear mixed effects models (GLMMs) accounting for within-group correlation across longitudinal data will then be applied.

Outcomes will be modeled as a function of group assignment and time since intervention. The association between outcomes and time will be explored visually using scatterplots and lowess smoothers. Restricted cubic splines will be added to reflect deviations from linearity. GLMM with random intercepts for peer group and study participant will be used to account for the hierarchical structure of the data: peer group, participants nested within peer group and assessments nested within study participants. If siblings enter the study together during the same wave, they will be randomized to the same study group (intervention or control) to limit contamination. In this case, analyses will be adjusted to take into account intra-sibling correlation as well. Missing data will be handled as follows: (1) document reason(s) for missing data to inform model development; (2) assess treatment dropouts to do intent-to-treat analysis; (3) conduct sensitivity analysis to compare inferences that are based on different plausible reasons for missingness [32, 33].

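### The secondary sexual-behaviour outcomes are compared only among sexually active youth, a group that RCL is meant to shrink, so the comparison can be biased in either direction

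*Protocol article*

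**What the plan says.** Under Secondary Outcome Measures the article sets the analysis population: "Secondary outcome variables will be examined among sexually active participants including condom use at last sex". The same sentence applies it to "number of sexual partners, sex without a condom in the last 3 months and sex without contraception in the last 3 months". On the size of the subset it says: "It is expected that 20-25% of study participants will be sexually active". No time point is attached to being sexually active.

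Sexual initiation is a primary endpoint. Trial Design lists "delayed sexual initiation 9 months post-intervention". The sample size section hypothesises that "the intervention group will have a lower proportion of participants who initiate sex, compared to controls, at study end line". Primary Outcome Measures explains how the primary variables were selected: "These variables were chosen because they are applicable to all study participants". No such reason is given, or could be given, for the secondary outcomes as they are now defined.

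**The concern.** Randomisation makes the two arms comparable as whole groups. It does not make subsets comparable when membership is decided after randomisation and is influenced by treatment.

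If RCL delays sex in some youth, the active youth in the control arm include those whom RCL would have kept out, and the active youth in the RCL arm do not. The two subsets then differ in kind. Condom use, contraception and partner numbers can differ between them even if RCL changed none of these behaviours in anyone. The more RCL succeeds on its own initiation hypothesis, the harder the secondary results are to interpret.

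These outcomes are the planned measures of protective behaviour, close to the unprotected sex and unintended pregnancy that the Background names as the trial's target. A false harm or a false benefit here would mislead the community that has to decide whether to adopt the programme.

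**Working it through.** **The plan's own figures.** The article states no power, expected rate or detectable difference for the secondary outcomes, so there is none to reproduce. It gives the expected active share (20-25%), the sample size (567 youth) and the maximum attrition (25%). From these, 567 × 0.20 = 113 and 567 × 0.25 = 142 active youth, or 85 and 106 after multiplying by 0.75.

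**Model.** Suppose RCL changes no one's condom use and only prevents some youth from becoming active. Let a be the share of youth active under either programme, with condom use A. Let p be the share active under control but not under RCL, with condom use P under control.

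- Condom use among active controls: (a·A + p·P)/(a + p)
- Condom use among active RCL youth: A
- Apparent effect (RCL minus control): s·(A − P), where s = p/(a + p)
- Unprotected sex over all randomised youth: a(1 − A) + p(1 − P) in controls and a(1 − A) under RCL

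**Assumed inputs.** a = 0.20, p = 0.05 and A = 0.50, with P varied. The control active share of 25% is the top of the article's range. The split and the condom-use rates are assumptions, because the article gives none. Here s = 0.05/0.25 = 0.20.

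| P | Condom use, active controls | Condom use, active RCL | Apparent effect | Unprotected, all controls | Unprotected, all RCL |
|---|---|---|---|---|---|
| 30% | (0.10 + 0.015)/0.25 = 46% | 50% | +4 points | 13.5% | 10% |
| 50% | (0.10 + 0.025)/0.25 = 50% | 50% | 0 | 12.5% | 10% |
| 80% | (0.10 + 0.04)/0.25 = 56% | 50% | -6 points | 11% | 10% |

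In every row the true effect on condom use is nil and the true effect on unprotected sex is a reduction. The comparison within the subset shows a benefit, nothing or a harm, depending only on P. The comparison over all randomised youth has the right direction each time.

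**Sensitivity.** The bias grows with s. If the active share falls from 25% to 15%, s = 0.10/0.25 = 0.40.

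- A = 45%, P = 75%: 0.40 × (−0.30) = -12 points.
- A = 60%, P = 30%: 0.40 × 0.30 = +12 points.
- A = 50%, P = 75%: active controls are at 0.60 × 0.50 + 0.40 × 0.75 = 60%, against 50% under RCL, a bias of -10 points. A real 5-point gain in condom use would appear as 55% against 60%, that is -5 points.

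If p = 0, or if A = P, the bias is zero.

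**The case against.** **Timing.** The article never dates sexual activity. If baseline status were meant, the subset would be fixed before randomisation and the concern would fall. That possibility stands. But the outcomes are follow-up behaviours, two of them with 3-month recall, and the text speaks of youth who will be active, so follow-up status is the natural reading.

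**Size.** Every rate in the illustration is assumed. The only route into the bias that the documents state is delayed initiation, and youth who had already begun before the trial do not come through it. Their share is not given. This stands: a reader might infer that RCL will look harmful, and the documents do not support that or any other sign.

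**Intent-to-treat.** A reader might also infer that the plan breaks its own promise: "Study hypotheses will be initially tested under an “intent-to-treat” model in which data are analyzed according to randomization assignment". The documents do not support that. The hypotheses set out in the sample size section concern condom use self-efficacy and sexual initiation, the impact evaluation that follows refers to primary outcomes, and members of the subset would still be analysed by assigned arm. The restriction is openly declared.

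**Importance.** The primary outcomes apply to every participant, and the reduced significance level and all power statements concern them. No primary conclusion depends on this point.

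**Precision.** One might argue that using all youth is far more precise, with a standard error of about 0.03 against 0.10 in the subset, before any design effect. These are on different scales. A 10-point gain among the 25% who are active is 2.5 points over everyone, about 0.8 standard errors against 1.0 in the subset. The change removes selection; it does not buy power.

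**Conclusion.** The point holds for the secondary outcomes, provided that sexual activity is determined at follow-up. The comparison then conditions on a state that the trial expects treatment to change, and it is not protected by randomisation. The direction is unknown. Under the main assumed inputs the false difference in condom use is about +4 to -6 points, and a larger assumed effect on activity widens it to ±12. It vanishes if initiation is unaffected or if prevented and always-active youth use condoms equally. The illustration assumes that RCL only prevents activity and never prompts it, and it ignores loss to follow-up.

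The severity is should-fix. The finding does not show that the primary analyses are unsound or that the secondary results will err towards harm.

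**What to change.** Make the main between-arm comparison of each secondary outcome over all randomised youth:

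- any condomless sex over the past 3 months, with no sex counted as no;
- any sex unprotected by contraception over the past 3 months, with no sex counted as no;
- number of partners, with none counted as 0;
- condom use at last sex recast as unprotected last sex within a stated follow-up window, yes or no, with no sex in the window counted as no.

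The window in the last item matters. Restricting condom use at last sex to youth active at baseline would not be enough, because for those with no sex since the programme the last occasion predates it, and dropping them would again select on behaviour after randomisation.

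Label analyses among youth sexually active at follow-up as descriptive. Base any subgroup analysis on sexual activity at baseline, and say so.

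The cost is wording in the analysis plan and recoding of behaviours the questionnaire already covers, assuming that its items can place the last occasion inside the window. The article reports that recruitment was still open, so this could be settled before results are seen. The drawback is a change in the question answered. The all-youth outcomes combine abstinence with protection and overlap with the initiation primary, and reports must describe them that way.

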### Sample Size Calculation and Statistical Analysis

Our goal is to recruit 567 youth (and their parent/trusted adult) balanced within two age groups (11–12, 13–15 and 16–19), for a total of 1134 participants (567 youth and 567 parents/trusted adults). We expect a maximum attrition rate of 25%, based on past rates in similar evaluations [18, 19, 29, 30].

Sample size estimates were based on the variables of condom use self-efficacy and sexual initiation because these confirmatory research questions apply to all study participants, and prior studies have shown them to be associated with reductions in risky sexual behavior, teen pregnancy and STI incidence [23]. We hypothesize that the RCL intervention will increase condom use self-efficacy in the intervention group compared to the control group and that the intervention group will have a lower proportion of participants who initiate sex, compared to controls, at study end line.

The condom use self-efficacy scale ranges from 1–5. Our pilot trial [18] provided data on the condom use self-efficacy score among the control group (mean = 2.6, SD = 1.0), degree of intra-team correlation (“k” = 0.12) and potential loss to follow-up over 9 months (20% average reduction in team size, i.e., from 9 down to 7.2 youths). Although this trial will utilize individual randomization, the intervention will be carried out with teams of 8–12 participants each, which will require accounting for intra-team correlation.

We will use the average of two follow-up measures of condom use self-efficacy per participant (intra-measure correlation = 0.7) to reduce error in outcome measurement [31]. To achieve 90% power to detect a theoretically meaningful between-group difference of 0.47 points on this scale over 9 months post-intervention, ~32 teams per study arm will be required. Thus, we will enroll and randomize a total of *n* = 284 participants per study arm (32 teams/arm *9 participants/team), for a total sample size of *n* = 567 participants. We have reduced the significance level used in sample size calculations to 0.0125 to account for multiplicity corrections during analyses. This same sample size will be sufficient to detect a 19.7% between-group difference, with 80% power and 0.0125 significance level, in the percent of participants who report ever having had sex. This estimate is conservative based on our past retention rates and accounts for up to 25% loss to follow-up, while adjusting for the intra-team correlation.

This sample size will also be able to detect meaningful differences between the intervention and control groups with at least 80% power, given the assumptions listed above: 6.7% between-group difference in reproductive/sexual health knowledge score [estimating a mean score (SD) of 76% (16%) in the control group] and 20.5% between-group difference in intention to use a condom at next sex (estimating 55% in the control group).

Study hypotheses will be initially tested under an “intent-to-treat” model in which data are analyzed according to randomization assignment. We will then conduct “completer analyses” on those subjects finishing at least two-thirds of the 9 intervention sessions. Intervention impact will be evaluated by comparing primary study outcomes between intervention and control groups across the three time points: baseline, 3 and 9 months post-intervention. Initially, summary scores of outcomes will be stratified by participation in the intervention versus control groups and by time point and compared using chi-square tests (for binary or categorical outcomes), t-tests and analysis of variance (for continuous outcomes). The equivalence of the two study groups at baseline will be compared across a range of background variables. Generalized linear mixed effects models (GLMMs) accounting for within-group correlation across longitudinal data will then be applied.

Outcomes will be modeled as a function of group assignment and time since intervention. The association between outcomes and time will be explored visually using scatterplots and lowess smoothers. Restricted cubic splines will be added to reflect deviations from linearity. GLMM with random intercepts for peer group and study participant will be used to account for the hierarchical structure of the data: peer group, participants nested within peer group and assessments nested within study participants. If siblings enter the study together during the same wave, they will be randomized to the same study group (intervention or control) to limit contamination. In this case, analyses will be adjusted to take into account intra-sibling correlation as well. Missing data will be handled as follows: (1) document reason(s) for missing data to inform model development; (2) assess treatment dropouts to do intent-to-treat analysis; (3) conduct sensitivity analysis to compare inferences that are based on different plausible reasons for missingness [32, 33].

Current funding for this evaluation supports data collection through 9 months post-intervention. If additional funding is secured, we will extend data collection to 12, 24 and 36-months post-intervention and collect medical chart data to track incidence of STIs and pregnancy. If additional funding is secured, gift cards in amounts commensurate with the time required to complete additional follow-up assessments will be given.

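### The sample-size figures do not fit together: 32 × 9 is 288 per arm, not 284, and no one reading of the 0.12 that keeps the stated two-measure average gives both about 32 teams and the 6.7-point knowledge difference

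*Protocol article*

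**What the plan says.** All the figures are in the protocol article, under Sample Size Calculation and Statistical Analysis.

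- **Enrolment target:** "Our goal is to recruit 567 youth", with a maximum expected attrition of 25%.
- **Pilot inputs for the self-efficacy scale:** "condom use self-efficacy score among the control group (mean = 2.6, SD = 1.0"; "degree of intra-team correlation (“k” = 0.12"; and a "20% average reduction in team size, i.e., from 9 down to 7.2 youths".
- **Outcome used for sizing:** the mean of two follow-up measures per participant, with a correlation of 0.7 between them.
- **Target:** "To achieve 90% power to detect a theoretically meaningful between-group difference of 0.47 points on this scale". On alpha: "We have reduced the significance level used in sample size calculations to 0.0125".
- **Result:** about 32 teams per arm, then "284 participants per study arm (32 teams/arm *9 participants/team", for 567 in total.
- **Closing claim:** the estimate "accounts for up to 25% loss to follow-up".
- **Other outcomes, on the same assumptions with at least 80% power:** a knowledge difference of 6.7 points (control mean 76%, SD 16%) and a condom-intention difference of 20.5 points (control 55%).

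**The concern.** The enrolment number is shown as the product of two factors, and it is not that product. Working back from the listed inputs, about 32 teams appears under one set of assumptions and not under others, because two matters are left open. The symbol *k* is often used for a between-cluster coefficient of variation, although the text calls it a correlation. It is also unclear whether the averaging described actually entered the calculation. The retained team size of 7.2 reflects 20% loss, while the closing sentence claims cover to 25%.

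A reader therefore cannot confirm the 90% power for one of the two outcomes that set the sample size, or tell which assumptions lie behind the detectable differences given for the other outcomes.

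**Working it through.** **Assumption.** The protocol does not say whether alpha is one- or two-sided. I take it as two-sided: z for 0.0125 is 2.498, z for 90% power is 1.282, and the squared sum is 14.283. One-sided alpha does not reproduce 32 on either of the readings below that do so two-sided; it gives 27 to 29 teams.

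**1. The product.** 32 × 9 = 288 per arm, and 64 × 9 = 576 in total. The stated total is 567 = 63 × 9, or 31.5 teams per arm. 567 / 2 = 283.5, which rounds to 284.

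**2. Teams per arm with 0.12 as an intra-team correlation.** Teams = 2 × 14.283 × V / 0.47², where V is the variance of a team mean, SD = 1.0 and m = 7.2.

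- Single measure: V = [1 + 6.2 × 0.12] / 7.2 = 1.744 / 7.2 = 0.2422, giving **31.3 teams**. This reproduces the plan's figure.
- Average of two, with the variance factor (1 + 0.7) / 2 = 0.85 applied to the whole variance: V = 0.85 × 0.2422 = 0.2059, giving **26.6, so 27 teams**.
- Average of two, with the reduction applied only to the within-team part: V = 0.12 + (0.85 − 0.12) / 7.2 = 0.2214, giving **28.6, so 29 teams**.

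**3. Teams per arm with 0.12 as a coefficient of variation.** The intervention mean is 2.6 + 0.47 = 3.07.

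Teams = 1 + 14.283 × [2 × 0.85 / 7.2 + 0.12² × (2.6² + 3.07²)] / 0.47² = 1 + 14.283 × 0.4692 / 0.2209 = **31.3**.

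This also reproduces the plan's figure, now with the averaging kept.

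**4. Check against the knowledge outcome.** Control mean 76%, SD 16%, 80% power (squared sum 11.151), 31.5 to 32 teams per arm, 6.75 to 7.2 per team.

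| Reading of 0.12 | Detectable difference (plan: 6.7) |
|---|---|
| Correlation, single measure | 6.6 to 6.7 points |
| Correlation, average of two | 6.1 to 6.4 points |
| Coefficient of variation, average or single | 9.5 to 9.8 points |

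The coefficient-of-variation figure is large because 0.12 × 76 implies a between-team SD of about 9 points. Condom intention (plan: 20.5) points the same way: 19.2 to 19.7 points with a correlation, 16.4 to 16.9 with a coefficient of variation.

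**5. Loss of 25%.** m = 9 × 0.75 = 6.75. The two readings that gave 31.3 teams now give 32.4 (correlation, single measure: design effect 1.69) and 32.4 (coefficient of variation, averaged). The correlation readings with averaging give 27.5 to 29.5.

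**6. Power for 0.47 points at 567 youth (31.5 teams per arm).**

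| Reading | 20% loss | 25% loss |
|---|---|---|
| Correlation, average (whole variance) | 94.7% | 93.9% |
| Correlation, average (within-team part only) | 92.9% | 92.0% |
| Correlation, single measure | 90.2% | 89.1% |
| Coefficient of variation, average | 90.2% | 89.1% |

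**The case against.** The strongest reply is that everything agrees up to rounding. Teams are given as approximate, and an unrounded 31.5 per arm yields 567 in total, 283.5 (shown as 284) per arm, and about 32 when displayed. That is a plausible origin for the numbers, and the gap is only 1.6% in total (576 against 567), worth about half a point of power. It stands as an explanation, but the printed product is still wrong.

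The second reply is that *k* as a coefficient of variation returns about 32 teams with every stated input, averaging included. This is correct, and it means that 27 cannot be presented as the right number. A reader might infer that 27 teams is what the plan should have said, but that takes both the correlation reading and the 0.85 factor on the whole variance; with the reduction confined to the within-team part it is 29. The coefficient-of-variation reading does not rescue the section, however. The text calls 0.12 a correlation, and that reading misses the plan's own knowledge difference by about 3 points. A correlation with a single measure matches both figures, but it sets aside the averaging that the plan says it will use for self-efficacy.

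The third reply is that 20% and 25% do not conflict. That stands: one is the pilot average and the other a stated maximum, so there is no contradiction. What remains is that the only team size shown for the calculation corresponds to 20%.

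A reader might also infer that 567 youth cannot fill 64 teams. The protocol allows teams of 8 to 12, and 567 / 64 = 8.9, so they can.

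**Conclusion.** The sample-size paragraph is not internally consistent and should be restated. The product is wrong by 4 youth per arm and 9 in total. With 0.12 as the intra-team correlation that the text names, the stated averaging leads to 27 to 29 teams and about 92% to 95% power at 567 youth, while the plan's own 32 teams and 90% belong to a single measure. With 0.12 as a coefficient of variation, the team count is recovered and the knowledge difference is not. At 25% loss, the readings behind about 32 teams fall short by roughly one point of power (89.1%).

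These results assume two-sided alpha, equal team sizes and normal approximations. They also assume that the 0.12 carries over to knowledge and intention, as the plan's reference to the same assumptions implies.

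It would be wrong to conclude that the trial is under-sized. On the readings tabulated, power stays between about 89% and 95%, and on the reading closest to the text the trial is somewhat larger than needed. The defect lies in the stated derivation, not in the adequacy of enrolment.

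**What to change.** - Replace the product by 63 teams of 9 in total (567 youth, 31.5 teams per arm on average). If 32 teams per arm is kept, state 288 per arm and 576 in total.
- Say whether 0.12 is an intraclass correlation or a between-team coefficient of variation.
- For each outcome, say whether the calculation uses one follow-up measure or the average of two and, if the average, which variance component it reduces.
- State whether alpha is one- or two-sided.
- Use the 25% loss (6.75 per team) throughout.
- On that single basis, restate the power for 0.47 points at 567 youth and the detectable differences for sexual initiation, knowledge and condom intention.

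The cost is a text correction and a short recalculation. The stated power may move from 90% to about 89%, or up to between 92% and 94%, depending on the definitions given (25% loss, readings tabulated above). No extra enrolment is needed.
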